### Measures

#### Screening phase

The screening phase takes place during the hospitalization or consultation in a neurosurgical unit during which the diagnosis of CSDH is confirmed. A standard clinical examination is performed to ensure that the patient meets the selection criteria of the study. The initial CT scan (performed onsite or in another hospital depending on the origin of the patient) completes this initial patient screening. If the patient is eligible, written informed consent from the patient or a representative (if the patient’s cognitive state does not allow informed decision) is necessary before enrollment.

#### Baseline data collection

The following information is collected before initiation of the treatment:

Patients’ characteristics: sex, age, weight, height, major medical history (including chronic alcoholism), ongoing medications affecting hemostasis (anticoagulants and platelet antiaggregants), and symptoms that led to the diagnosis of CSDH (persistent headache, repeated falls, balance disorders, attention and memory disorders, muscular weakness, motor or sensitivity disorders).

The clinical assessment includes: blood pressure measurement, neurological examination (Glasgow Coma Scale (GCS) score, diameter and symmetry of the pupils, presence of a focal neurological deficit), functional scales (modified Rankin Scale, IADL and MMSE assessments, quality of life (SF12 scale) and comprehensive review of the overall clinical assessment score with the ASA (American Society of Anesthesiologists).

#### Follow-up

Patients are followed up for a period of 6 months, and are evaluated at 1, 3 and 6 months. At days 0, 7, 14 and 21 and at the 1-month visit, plasma sodium, potassium and fasting glucose are measured. Fasting plasma cortisol at 8 a.m. is measured 2 days after the end of the treatment with corticosteroids (at day 23). Patients will undergo interval cerebral CT scans to evaluate their CSDH at the following intervals: screening visit, M1, M3 and M6 (Fig. 1). This biological surveillance allows the detection of any electrolyte or glycemic impairment that could occur with steroid treatment.

**Fig. 1 Fig1:**
[figure not shown]
Study flow chart. *Plasma sodium, potassium, and fasting glycemia/**fasting plasma cortisol

### Statistical analysis

Statistical analysis will be performed on all evaluated patients (intention-to-treat analysis in the methodology/biometrics unit of the Clinical Investigation Centre Inserm 1414 of Rennes. The statistical significance will be considered to be *p* values < 0.05 for all analysis.

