### Study population

Our hypothesis is that 80% of the patients taking placebo will be operated on at 1 month. A total sample size of at least 202 patients (142 events) is required to achieve 90% power to detect a decrease in the rate of surgery to 60% (hazard ratio of 1.756) with methylprednisolone, using a two-sided log-rank test with a 0.05 significance level assuming that the hazards are proportional (nTerim, V1.1, Statistical Solutions Ltd., Cork, Ireland).

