#### Analysis of the primary endpoint

Time to surgical treatment (i.e., the delay of occurrence of surgical treatment) of the CSDH at 1 month will be compared between the two groups with the log-rank test. Two interim analyses after inclusion of one third and two thirds of the patients, and one final analysis are planned. Stopping rules will use the alpha spending function with the O’Brien-Fleming boundary. The cumulative values of alpha for each analysis are: 0.00021 at the first analysis, 0.01202 at the second analysis and 0.04626 at the final analysis (nTerim, V4.0, Statistical Solutions Ltd., Cork, Ireland). The trial will be stopped early if the significance of the log-rank test is below these alpha values.

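### The general 0.05 rule and the group-sequential value of 0.04626 compete for the final primary test, and the per-look levels are mislabelled as cumulative alpha

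*Protocol article*

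**What the plan says.** The opening paragraph of Statistical analysis in the protocol article sets one rule: "The statistical significance will be considered to be *p* values < 0.05 for all analysis". It makes no exception for the primary endpoint. The sample size under Study population rests on the same figure, "using a two-sided log-rank test with a 0.05 significance level", and does not mention interim looks.

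The subsection Analysis of the primary endpoint then describes a group-sequential test. On timing it says: "Two interim analyses after inclusion of one third and two thirds of the patients, and one final analysis are planned". On the boundary: "Stopping rules will use the alpha spending function", of O'Brien-Fleming type. On the levels: "The cumulative values of alpha for each analysis are: 0.00021 at the first analysis, 0.01202 at the second analysis and 0.04626 at the final analysis". One sentence puts these levels to use: "The trial will be stopped early if the significance of the log-rank test is below these alpha values". No sentence says what the final p-value is compared with if the trial runs to its end.

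**The concern.** There are two separate faults.

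First, the final log-rank test falls under two rules. The general rule gives 0.05 and the primary-endpoint subsection gives 0.04626. A final p-value between them is significant under one and not under the other. Two interim looks have already used part of the 5%, so a final test at the full 0.05 would exceed the error rate on which the trial was sized. If the choice is left open, it could be made once the p-value is known.

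Second, the label is wrong. Cumulative alpha under a spending function is the total error used up to a given look, and it must reach the overall level at the last look. A list that ends at 0.04626 cannot be the cumulative spend of a 0.05 design. A statistician who fed the values into software as cumulative spend would obtain different boundaries from those intended.

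**Working it through.** **Inputs from the article.** Two-sided overall level 0.05 (Study population); three looks at one third, two thirds and all of the patients; O'Brien-Fleming-type spending; stated levels 0.00021, 0.01202 and 0.04626 (all Analysis of the primary endpoint).

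**Assumption.** The information fractions are t = 1/3, 2/3 and 1. The article times the looks by patients included, whereas the information in a log-rank test is the number of events.

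**Step 1: cumulative alpha.** The O'Brien-Fleming-type spending function at two-sided 0.05, with 0.025 in each tail, is

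α(t) = 4 × [1 − Φ(2.2414/√t)], where 2.2414 is the 0.9875 quantile of the standard normal.

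- t = 1/3: 0.000207
- t = 2/3: 0.012097
- t = 1: 0.05000

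**Step 2: reproduce the stated values.** Solving for the boundaries by recursive numerical integration, so that the crossing probability up to each look equals α(t):

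| Look | z boundary | Nominal two-sided p | Stated in the article | Cumulative alpha spent |
|---|---|---|---|---|
| 1 | 3.710 | 0.00021 | 0.00021 | 0.00021 |
| 2 | 2.511 | 0.01202 | 0.01202 | 0.01210 |
| 3 | 1.993 | 0.04626 | 0.04626 | 0.05000 |

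The stated values match the nominal column to five decimals at every look. They match the cumulative column only at the first look, where the two are the same by definition. Two alternatives were tried and neither fits: the spending function without splitting alpha by tail gives nominal levels 0.00069, 0.01610 and 0.04388, and the classical O'Brien-Fleming boundary gives 0.00052, 0.01411 and 0.04507.

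**Step 3: overall two-sided type I error**, with the stated interim levels and one of the two candidates at the final look:

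- 0.04626 at the final look: 0.0500
- 0.05 at the final look: 0.0535

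The difference is 0.0535 − 0.0500 = 0.0035, or 0.35 percentage points. Under the null hypothesis this is the probability of reaching the final look and landing between 0.04626 and 0.05.

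**Step 4: does the sample size depend on the choice?** Study population assumes 80% operated on with placebo and gives the effect as "to detect a decrease in the rate of surgery to 60% (hazard ratio of 1.756) with methylprednisolone". The hazard ratio reproduces: ln(0.2)/ln(0.4) = 1.756. Freedman's formula with 90% power gives 140 events and 140/0.70 = 200 patients, close to the stated 142 and 202. With 142 events the drift is √142 × (1.756 − 1)/(1.756 + 1) = 3.27. Power is then about 0.905 for a single test at 0.05, and about 0.902 for the three-look design with the stated levels. The sample size is not materially affected.

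**The case against.** The strongest reply is that a specific rule overrides a general one. The primary-endpoint subsection gives a value for the final analysis, and an ordinary reader would apply it there and keep 0.05 for everything else. Much of this stands. A valid set of thresholds can be recovered from the article, and used as direct p-value limits the three numbers hold the error at 5.00%. It does not settle the matter, because the sentence that turns the numbers into a decision rule speaks only of stopping early, while the general rule says that it covers all analyses.

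Three stronger readings are tempting, and the article does not support them.

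- *The primary test has no valid threshold, or the values are misused.* The article compares the log-rank p-value directly with the listed values, which is the correct use of nominal levels. The numbers are right; the label is wrong, and the exception to the general rule is unwritten.
- *Only 0.0463 of alpha is spent in total.* Taken literally as cumulative spend, the list would imply a final nominal level of about 0.0423. That conflicts with the way the article applies the values and with the 0.05 level under Study population.
- *The type I error could reach 10.7%.* That is the figure if 0.05 were applied at all three looks. It requires ignoring the interim levels of 0.00021 and 0.01202, to which the article explicitly ties early stopping. The Data Safety Monitoring Board section mentions interim significance without naming a threshold, but this does not displace the levels stated for the primary endpoint.

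**Conclusion.** The concern holds as an unresolved conflict over the final threshold together with a wrong label. It is not an error in the calculated boundaries. The article does not fix whether 0.05 or 0.04626 decides the final primary test. The realistic consequence is a two-sided type I error of about 5.35% instead of 5.00%, and a changed conclusion only if the trial reaches its final look with a p-value between 0.04626 and 0.05. The wrong label changes no decision as long as the values are compared directly with p-values, as the article does at the interim looks.

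The figures rest on information fractions of exactly 1/3, 2/3 and 1. Events follow inclusions with a delay, so the actual fractions, and with them the correct levels, may differ somewhat. This should be fixed because it concerns the success criterion of a phase III trial; its size does not make it critical.

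**What to change.** In the opening paragraph of Statistical analysis, limit the 0.05 rule, for example: *Two-sided p-values below 0.05 are considered significant, except for the primary endpoint, which is tested only against the group-sequential levels given below.*

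In Analysis of the primary endpoint, replace the description of the three values, for example: *The nominal two-sided significance levels are 0.00021, 0.01202 and 0.04626 at the first, second and final analysis; the corresponding cumulative alpha spent is 0.00021, 0.01210 and 0.05000.*

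Add one sentence on the final test: *If the trial is not stopped early, the final log-rank test is judged against 0.04626, or against the level that the spending function gives at the event fractions actually observed.*

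The cost is a few sentences. The number of looks, the boundary and the sample size stay as they are. The final level of 0.04626 already stands in the article, so nothing becomes stricter than the design already intends. The change should be made before any unblinded result is seen.

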#### Analysis of the primary endpoint

Time to surgical treatment (i.e., the delay of occurrence of surgical treatment) of the CSDH at 1 month will be compared between the two groups with the log-rank test. Two interim analyses after inclusion of one third and two thirds of the patients, and one final analysis are planned. Stopping rules will use the alpha spending function with the O’Brien-Fleming boundary. The cumulative values of alpha for each analysis are: 0.00021 at the first analysis, 0.01202 at the second analysis and 0.04626 at the final analysis (nTerim, V4.0, Statistical Solutions Ltd., Cork, Ireland). The trial will be stopped early if the significance of the log-rank test is below these alpha values.

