#### Primary endpoint

The primary evaluation criterion is the delay of occurrence of surgical treatment (censored criteria) of the CSDH at 1 month. One month has been chosen for assessing the primary endpoint because most surgical interventions, if needed, are expected to occur during the first month following the diagnosis of CSDH. Patients who are nonevaluable for the primary endpoint (death, loss to follow-up, etc.) will be censored at the date of death or the latest news.

Criteria for recourse to surgery are (one is sufficient): lack of clinical improvement at 1 month, immediate or delayed clinical deterioration, appearance of radiological signs of severity (midline shift >5 mm, uncal transtentorial herniation).

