### Description of the measures taken to reduce and prevent bias

#### Randomization

The randomization list will be prepared by the Biometrics Unit of the Clinical Investigation Centre Inserm 1414 of Rennes. Randomization will be stratified by center and equilibrated at a 1:1 ratio. After verification of selection criteria during the screening phase, the investigator will proceed to the randomization of the patient the day of baseline (D0). The investigator sends the order-processing request to the pharmacist of his center. The pharmacist attributes treatment to the patient according to their list in chronological order and informs the coordinating centre by faxing the completed order.

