As mentioned above, one of the weaknesses of our work is the lack in the academic literature of studies describing the natural history of CSDH without treatment; some may claim that some cases of CSDH without clinical and neurological signs of severity could heal spontaneously. Another issue concerns the inclusion of patients with cognitive disorders. Confusion and dementia might be difficult to distinguish in an acute context, so the questioning of the relatives is of particular importance. We still wanted to include patients with doubtful or mixed semiology, who pose the greatest ethical dilemmas in everyday practice. A medical alternative to surgery in these cases would be of particular interest considering the invasiveness of surgery for that fragile population. However, corticosteroids might have psychic side effects liable to destabilize the mental status of such patients.

Another point of debate is the duration of corticosteroid therapy. After discussion with the endocrinology team of our establishment and on the basis of the academic literature [36–39], we decided to limit the treatment to 3 weeks. Indeed, after this period the risk of adrenocortical insufficiency induced after the discontinuation of corticosteroids increases significantly. Usually, adverse effects associated with corticosteroids predominantly occur during consumption of these medications over several weeks or months. We also decided to lower the inclusion boundary to a GCS score of 13. For those patients with a GCS score of 13 and, therefore, mild vigilance disorders, we recommend close monitoring in neurosurgical departments during the first days or the first week of treatment in order to assess the effectiveness of the treatment and possibly perform surgery in case of clinical deterioration. We left the choice to each of the investigators about the choice of timing to perform a secondary surgery.

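### Randomisation is stratified by centre but the primary log-rank test is named without centre, which is conservative and gives up some power if centres differ in their readiness to operate

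*Protocol article*

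**What the plan says.** Under Randomization, the article states: "Randomization will be stratified by center and equilibrated at a 1:1 ratio".

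Under Analysis of the primary endpoint, time to surgery "of the CSDH at 1 month will be compared between the two groups with the log-rank test". The two interim looks and the early-stopping rule in the same paragraph refer to that test. Centre is not mentioned.

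Under Study population, the trial is sized "using a two-sided log-rank test with a 0.05 significance level assuming that the hazards are proportional", again without strata.

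Adjustment appears once, under Analysis of other criteria. It is optional and depends on imbalance at inclusion.

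On what drives the event, the Discussion says: "We left the choice to each of the investigators about the choice of timing to perform a secondary surgery". The section on authorised and unauthorised medicinal products leaves the handling of drugs affecting haemostasis to each centre's habits.

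**The concern.** Stratified randomisation balances the arms within each centre. Chance differences between arms in centre mix are therefore largely removed by design. An unstratified log-rank test estimates its variance as if they were still there. If centres differ in the hazard of surgery, the standard error is too large for the randomisation actually used, and the test rejects less often than its nominal level.

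This could matter here because the event is a clinical decision whose timing is partly local. The trial would pay for balance by centre and then not use it. At stake is efficiency: some of the planned power at the final analysis, and some of the chance of crossing a boundary at an interim look. The optional adjustment would not repair this even if it were extended to the primary endpoint. It is triggered by baseline imbalance, and stratification prevents imbalance by centre.

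**Working it through.** **Inputs from the article (Study population, Primary endpoint).** Placebo: "Our hypothesis is that 80% of the patients taking placebo will be operated on at 1 month". Effect: a "decrease in the rate of surgery to 60% (hazard ratio of 1.756"). Size: "A total sample size of at least 202 patients (142 events) is required to achieve 90% power". The endpoint is time to surgery, censored at 1 month.

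**Step 1: the plan's own figures.**
- Hazard ratio: ln(0.2)/ln(0.4) = 1.756, as stated.
- Events (Freedman): [(1.756+1)/(1.756−1)]² × (1.960+1.282)² = 139.5, so 140.
- Average event rate: (0.80+0.60)/2 = 0.70. Patients: 140/0.70 = 200.
- The stated 202 patients give 202 × 0.70 = 141.4, so 142 events. Freedman power at 142 events is 90.5%.

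The sizing is reproduced closely (140 and 200 against 142 and 202). The formula used has no strata.

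**Step 2: simulation.** 202 patients; exponential times cut at 1 month; placebo rate averaging 80%; centre effects normal on the log hazard.

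Assumptions not in the article: 5, 10 or 20 centres of unequal size, permuted blocks of 4 within centre, and the between-centre SD. Each trial is analysed in a single look at two-sided 0.05, with 3,000 runs for power and 8,000 under the null. The Monte Carlo standard error near 90% power is √(0.9 × 0.1/3000) = 0.55 points, so differences below about 1 point carry little weight.

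What the SD means: the middle 80% of centres operate on about 68–91% of placebo patients at SD 0.3, 60–96% at 0.5 and 50–100% at 0.8.

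**Step 3: within-centre hazard ratio fixed at 1.756, 10 centres.**

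| SD | Power, plain | Power, stratified | Type I, plain | Type I, stratified |
|---|---|---|---|---|
| 0 | 91.6% | 90.3% | 0.051 | 0.049 |
| 0.3 | 90.3% | 90.9% | 0.046 | 0.052 |
| 0.5 | 87.2% | 90.6% | 0.037 | 0.050 |
| 0.8 | 80.1% | 90.3% | 0.025 | 0.051 |

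At the article's final-look level of 0.04626 and SD 0.7, power is 80–82% plain and about 89% stratified. Null rejection is 2.7% and 5.1%.

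**Step 4: overall rates held at 80% and 60%, 10 centres.** The within-centre hazard ratio must then rise with the SD: exp(0.594) = 1.81 at SD 0.3, exp(0.646) = 1.91 at 0.5 and exp(0.756) = 2.13 at 0.8.

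| SD | Power, plain | Power, stratified |
|---|---|---|
| 0.3 | 92.8% | 93.0% |
| 0.5 | 94.3% | 96.1% |
| 0.8 | 95.8% | 98.8% |

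Across the settings tried, the plain test stays at about 91–96%, and stratifying adds about 0 to 3 points.

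**Step 5: when stratifying costs power.** With 20 centres and a within-centre hazard ratio of 1.756, plain against stratified power is 92.4% and 89.6% at SD 0, 90.3% and 88.4% at SD 0.3, and 87.0% and 88.8% at SD 0.5. At the second look (134 patients, level 0.012, 20 centres) it is 55% and 49% at SD 0, and 55% and 52% at SD 0.3.

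**The case against.** **The article is silent on strata rather than explicit.** It never says the test is unstratified. Stratification detail is often left to the statistical analysis plan, and sizing software commonly uses a plain test even when a stratified analysis is intended. This limits how firmly the point can be put. It does not remove it: the article names a plain test for sizing, primary analysis and stopping, and places adjustment only under other criteria.

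**A reader might infer that the trial misses its power target.** The documents do not support that. The hypothesis is stated as overall rates, and 1.756 is derived from them. On that hypothesis the plain test keeps its 90% (Step 4). The larger losses in Step 3 need a true overall effect smaller than the one planned.

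**A reader might infer that strong centre differences are built in.** They are plausible, no more. The Primary endpoint section sets common criteria for recourse to surgery, which limits local variation. The free choice of surgical technique is weak evidence, since it comes after the decision to operate.

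**A reader might infer a biased hazard ratio or too many false positives.** Neither follows. The marginal and within-centre hazard ratios are different estimands, and the marginal one lies nearer 1 because hazard ratios are non-collapsible. The error in the test is conservative.

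**The remedy is not free.** With many small, similar centres, stratifying loses power (Step 5). That stands, and it is the reason for a pooling rule.

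**Conclusion.** The point holds as a minor to moderate matter of efficiency. The primary test named does not use the factor on which randomisation is stratified. If centres differ in the surgery hazard, that test is conservative and gives up power; the validity of a positive result is not threatened.

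The size cannot be fixed from the article. Under the assumptions stated, with 10 centres and a within-centre hazard ratio of 1.756, the loss runs from about nothing at SD 0.3, through about 3 points at SD 0.5, to 7–9 points at SD 0.7. On the article's own overall rates the 90% target is met either way, and stratifying is worth about 0 to 3 points. The direction is firm; the size rests on an assumed number of centres and an assumed SD.

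**What to change.** State that the primary test is a log-rank test stratified by centre, used at both interim looks and at the final analysis. Small centres should be pooled by a rule fixed before unblinding. Report the hazard ratio from a Cox model stratified by centre, described as a within-centre estimand and not as a correction of bias. Keep the unstratified test as a sensitivity analysis. If the statistical analysis plan already stratifies, bring the paragraph on the primary endpoint into line with it, so that only one primary p-value is defined.

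The cost is one sentence in the plan. In power, it is about 1 point if 10 centres do not differ, and about 1 to 2 points with some 20 small, similar centres (nearly 3 in the run where 20 centres did not differ at all). The cost can be larger at an interim look, where strata are thinner. Pooling is meant to limit this, so the rule should be chosen with the actual number and size of centres in view.

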#### Secondary endpoints

Secondary evaluation criteria are: quality of life assessed by the Short Form 12-item (SF12) scale [28] at 1, 3 and 6 months; time to surgical treatment during the first 6 months (censored criteria); rate of surgical treatment of the CSDH at 1, 3 and 6 months; functional scales: daily living (Instrumental Activities of Daily Living; IADL) [29], cognitive (Mini-Mental State Examination; MMSE) [30] and the modified Rankin Scale [31] at 1, 3 and 6 months; plasma sodium, potassium and fasting glucose at days 0, 7, 14 and 21 and at 1 month; occurrence of adverse events potentially related to methylprednisolone (electrolyte disorders: hypokalemia, metabolic alkalosis, sodium retention (edema), hypertension, congestive heart failure; endocrine and metabolic disorders: Cushing’s syndrome, adrenal insufficiency, glucose disorders (impaired glucose tolerance, diabetes); gastrointestinal disorders: ulcer, perforation, gastrointestinal tract hemorrhage; skin disorders: acne vulgaris, purpura, hematoma, hypertrichosis; neuropsychological disorders: euphoria, insomnia, agitation, confusion, depression; ophthalmological disorders such as glaucoma); survival at 6 months; radiological improvement, defined by reduction of maximal thickness of hematoma and reduction of midline shift evaluated at 1, 3 and 6 months.

Subgroup analyses of all study endpoints will also be performed in subacute (less than 4 weeks old) and chronic (more than 4 weeks old) CSDH, and in patients treated or not treated with anticoagulant or platelet antiaggregant therapy.

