#### Analysis of other criteria

Student’s *t* test or a Mann-Whitney test if necessary will be used to compare quantitative variables. Quantitative criteria evaluated several times during the monitoring will be compared with repeated measures analysis of variance (ANOVA) with two factors (time, group). For qualitative criteria, a chi^2^ test will be used. For all these analyses, adjustments can be made in case of heterogeneity at inclusion.

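### The primary and stopping test is an unadjusted log-rank, so baseline severity data already collected go unused: a loss of efficiency, not of validity

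*Protocol article*

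**What the plan says.** Under Analysis of the primary endpoint, the protocol article says that time to surgery at 1 month "will be compared between the two groups with the log-rank test". The two interim looks and the final analysis apply their alpha limits to that same test. Study population sizes the trial on it too: "A total sample size of at least 202 patients (142 events) is required to achieve 90% power", "using a two-sided log-rank test with a 0.05 significance level assuming that the hazards are proportional".

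The event is surgery. Primary endpoint lists the criteria for it: no clinical improvement at 1 month, clinical deterioration, or "appearance of radiological signs of severity (midline shift >5 mm, uncal transtentorial herniation").

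Starting values of related quantities are available for every patient:
- Baseline data collection includes "neurological examination (Glasgow Coma Scale (GCS) score, diameter and symmetry of the pupils, presence of a focal neurological deficit").
- Follow-up places a CT at the screening visit.
- Secondary endpoints defines radiological improvement as "reduction of maximal thickness of hematoma and reduction of midline shift evaluated at 1, 3 and 6 months", which needs a screening value of each.

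Randomization is stratified by center only. The one sentence on adjustment, "For all these analyses, adjustments can be made in case of heterogeneity at inclusion", stands under Analysis of other criteria. It is optional and depends on observed imbalance.

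**The concern.** A patient who enters with a midline shift near 5 mm and a GCS of 13 starts closer to the surgery criteria than one with no shift and a GCS of 15. The protocol's Discussion treats GCS 13 patients as needing closer watch. If these baseline values predict surgery, a two-group log-rank leaves that variation unmodelled, and the treatment contrast it sees is pulled toward no effect relative to the contrast at a given baseline severity. Power that could be had without another patient is then given up.

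This matters most if the true effect is smaller than planned. The Discussion says that the 60% surgery rate rests on the team's own experience, and that the untreated course of the disease is poorly described.

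**Working it through.** **Inputs from the protocol article.** "80% of the patients taking placebo will be operated on at 1 month"; 60% under methylprednisolone; hazard ratio 1.756; two-sided 0.05; 90% power; 202 patients and 142 events; 1:1 allocation.

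**1. Reproduce the design.**
- Hazard ratio = ln(0.20)/ln(0.40) = 1.756, as stated.
- Freedman events = (1.960 + 1.2816)² × ((1 + 1.756)/(1 − 1.756))² = 139.5, so 140.
- Mean event proportion = (0.80 + 0.60)/2 = 0.70; 140/0.70 = 200 patients.
- The stated 202 patients give 202 × 0.70 = 141.4, so 142 events. The plan's figure reproduces closely.
- Power at 142 events is 90.5% (Freedman) or 91.9% (Schoenfeld).

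**2. Assumption not in the documents.** The prognostic strength of shift, thickness and GCS is not given. It is represented by one standard-normal baseline score X with hazard = λ(arm) × exp(γX), where γ is the log-hazard SD, ranged from 0 to 0.7. λ is set so that the marginal 1-month surgery rates stay at the stated values.

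**3. Simulation.** 202 patients, constant baseline hazard, censoring at 1 month, two-sided 0.05, no interim looks, 4,000 trials per row. The tests are the unadjusted log-rank and the Wald test of treatment in a Cox model with X.

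| γ (HR per SD) | 80% v 60%: log-rank → Cox | Gain (points) | 80% v 65%: log-rank → Cox | Gain (points) |
|---|---|---|---|---|
| 0 (1.00) | 92.7 → 92.3% | −0.4 | 74.8 → 74.2% | −0.6 |
| 0.3 (1.35) | 92.3 → 93.9% | +1.6 | 74.7 → 78.2% | +3.5 |
| 0.5 (1.65) | 93.5 → 97.2% | +3.7 | 74.8 → 84.1% | +9.3 |
| 0.7 (2.01) | 93.6 → 98.8% | +5.2 | 77.2 → 90.9% | +13.7 |

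With no treatment effect, both tests rejected in 4.6% to 5.3% of 3,000 trials.

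A separate set of 2,000 trials at 80% v 60% gave 92.0 → 94.0%, 93.4 → 96.7% and 93.3 → 98.8% at γ = 0.3, 0.5 and 0.7, which are gains of 2.0, 3.3 and 5.5 points. Monte Carlo error moves single entries by up to about a point, so the gains are best read as about 2, 3 to 4 and 5 points. At 80% v 65% they are about 4, 8 to 9 and 14 to 15 points.

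**4. Imperfect score.** If the measured score has 50% reliability, the gain at 80% v 60% falls to about 1 to 3 points over the same range of γ.

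**5. Where the gain comes from.** At γ = 0.5 the mean standard error of the log hazard ratio is 0.171 unadjusted and 0.173 adjusted, so it rises slightly. The mean absolute log hazard ratio moves from 0.58 to 0.65. The gain is in the size of the estimate, not in its precision.

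**6. Feasibility.** Treatment plus three covariates is four parameters. At one third of 142 events, about 47, this is 47/4 ≈ 12 events per parameter.

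**The case against.** The strongest reply is that nothing here is wrong. The log-rank is valid, the trial is sized on it, and its simulated power is above 90% in every row at the planned effect. All of that stands, and it makes this an efficiency point. An unseen analysis plan may add an adjusted model, but the protocol article itself fixes the primary and stopping test as unadjusted, so this is a stated choice rather than a detail left open.

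The gain may also be smaller than tabulated. Eligibility excludes shifts above 5 mm and leaves GCS at 13 to 15. Scheduled CTs after screening start at month 1. Lack of improvement at 1 month is not a threshold on shift or GCS, and investigators choose when to operate. Bilateral hematomas complicate both CT measures, and screening scans may come from another hospital. The simulation uses one correctly specified, perfectly measured score and is therefore a best case. These limits stand; the 50% reliability result is the more cautious guide.

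Three stronger readings are tempting but unsupported:
- A reader might infer that the trial is underpowered or its test unsound. The design reproduces and the test holds its level.
- A reader might infer that chance imbalance in shift or thickness biases the result. Under randomization it is random error, already covered by the 5% level.
- A reader might carry over the linear-model rule that adjustment shrinks variance by the squared correlation. It does not apply to a log hazard ratio, as step 5 shows.

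**Conclusion.** The point holds as a recommendation to use collected data better. At the planned effect the benefit is modest: about 2, 3 to 4 and 5 power points for log-hazard SDs of 0.3, 0.5 and 0.7, or about 1 to 3 points with a score of 50% reliability. The cost is under 1 point if the score is not prognostic. The benefit is larger if the true contrast is 80% versus 65%, which departs from the plan's own assumption.

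The direction depends on the covariates being prognostic. The link to the surgery criteria makes that plausible, but the protocol does not quantify it. All power figures are for a single fixed test at 0.05, constant baseline hazards and no interim looks.

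**What to change.** Before unblinding, amend Analysis of the primary endpoint so that the primary test is the treatment effect from a Cox model with screening midline shift, maximal hematoma thickness and baseline GCS. Fix the functional form of each in advance, with a stated rule for shift and thickness in bilateral hematomas. Adjustment should not depend on observed imbalance. Apply the existing interim and final boundaries to the model's z statistic for treatment. Report the unadjusted log-rank, Kaplan-Meier curves and 1-month surgery proportions alongside.

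The cost is wording in the protocol and analysis plan; no new data are needed. There is a small downside: the hazard ratio becomes conditional on baseline severity and depends on the covariate forms chosen. The same 80% and 60% that give 1.756 unadjusted correspond to about 1.81, 1.91 and 2.04 at log-hazard SDs of 0.3, 0.5 and 0.7. The unadjusted proportions are therefore needed beside it.
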